#### Independent variables and potential confounding factors

▪ Social and demographic parameters: age, gender, marital status, number of years of education, occupation, employment status, self-reported level of income (categorized in relation to the national average household income).

▪ Barriers to the use of CR services: poor health, work or financial constraints, lack of means of transportation.

▪ Health maintenance organization (HMO) affiliation and insurance coverage. We note that four national medical insurers/providers operate in Israel and a number of other medical insurance companies provide complementary services.

▪ Previous cardiovascular morbidity defined from the following question: "Did you undergo any previous cardiac procedures or cardiac related hospitalizations?"

▪ Co-morbidity defined from the questions: "Do you suffer from any other disease and/or handicap? If so, please specify the disease(s)/handicap and age at first occurrence"; "Have you been hospitalized in the last 12 months? If so, please specify the cause and month of each hospital admission."

▪ Medical treatment information: medications prescribed. This information is complementary to the information on self-reported conditions associated with cardiovascular disease (i.e., hypertension, diabetes mellitus, and hyperlipidemia) and other chronic diseases. Data was supplemented by information from medical files at hospitals.

▪ Severity of coronary disease: % ejection fraction (available for about half the patients), number of occluded vessels prior to CABG.

### Study population

#### Characteristics of participating patients

Of the 2811 CABG patients who underwent CABG surgery at the five participating cardiothoracic wards during the study period, 1024 (36%) were recruited to our study. Table 1 compares the demographic characteristics of the participants to the 2811 patients who underwent CABG surgery. As in the total post-CABG population, the proportion of women in our sample was approximately 24%; their mean age was about 5 years older than that of men.

**Table 1 T1:** Demographic characteristics of the post-CABG patients who participated in the study

Characteristic	All CABG patients n (%)	Participating CABG patients n (%)
Total number	2811 (100)	1024 (100)
Control arm	1401 (49.8)	520 (50.8)
Intervention arm	1410 (50.2)	504 (49.2)

% women	671 (23.9)	244 (23.8)

Age (mean and SD) [range]		
All	65.3+10.7 [30-92]	65.3+10.7 [37-91]
Women	69.7+10.2 [33-91]	70.0+9.2 [40-87]
Men	63.6+10.4 [30-92]	64.6+10.4 [37-91]

Ethnicity % **		
Jews - veteran Israeli citizen	1902 (64.1)	757 (73.9)
Jews - recent immigrants	589 (20.9)	216 (21.1)
Arabs	280 (13.0)	47 (4.6)
Other	40 (1.4)	4 (0.4)

Medical center		
Tel Aviv	777 (27.6)	363 (35.5)
Hadassah	497 (17.7)	146 (14.3)
Carmel	602 (21.4)	175 (17.1)
Asuta	351 (12.5)	154 (15.0)
Ramat Marpe	584 (20.8)	186 (18.2)

**** **Jews - veteran Israeli citizen are patients born in Israel or those who immigrated to Israel prior to 1989.

Jews - recent immigrants are patients who immigrated to Israel from the former Soviet Union since 1989, when about 750,000 Jews came to Israel during a short period of time

Arabs - Israeli Arab citizens

Other Israeli citizens not belonging to any of the above definitions.

Although veteran Israel citizens compose 64% of the population undergoing CABG surgery in Israel, they composed 74% of our sample. In contrast, the Arab population comprised 13% of the CABG population but only 4.6% of the study sample. This resulted mainly from the fact that the majority of Arabs reside in remote places, more than 30 kilometers from a cardiac rehabilitation center. Of those eligible to participate in the study, logistic difficulties, i.e. unavailability of an Arabic speaking interviewer, were the main causes for non-participation. There was no over-representation in refusal to participate among Arabs or any other ethnic group.

Differences in the five medical centers between the total number of patients undergoing CABG surgery and the number of participants in the study are also due, at least in part, to availability of interviewers. Patients who arrived at the hospital in the evening and underwent surgery early in the next morning were often not available for pre-surgical interviews.

#### Information regarding non-participants

To assess a possible selection bias, we collected information on all the patients who were not included in the study. A short semi-structured form including parameters such as age, sex, country of birth, ethnicity, medical center, and the reason for exclusion was filled.

### Data collection and analysis

#### Data collection, coding, and quality control aspects

To ensure standardization, periodic training was provided for interviewers. To achieve accuracy, data was collected in structured forms. Information was coded by a trained nurse who also carried out data entry and data quality assurance. All study questionnaires were reviewed for inaccuracies and inconsistent data entry. Quality assurance of personal interviews, as well as medical information, was carried out by the research coordinator. The study team convened at monthly meetings to review data outputs and discuss relevant issues, to standardize interviewing techniques, and to address potential problems.

#### Methods for statistical analysis

The analysis will constitute two parts according to the main study hypotheses: the first analysis will compare the intervention and the control arms to assess the impact of the intervention on the rate of CR uptake, and to assess the role of mediating factors. The second analysis will compare participants in CR programs and patients who did not participate in CR programs to evaluate the impact of CR on medical and psychosocial outcomes.

Univariate associations between the outcome measures in the comparison groups, and by various independent covariates, will be explored using the χ^2^-test, t-tests, and non-parametric procedures. To test for differences between two populations regarding continuous variables, we will use the unpaired t-test for normally distributed variables and the Wilcoxon rank sum test otherwise. To test for differences between two groups for various outcomes, adjusting for risk factors and potential confounders, we will use the generalized linear model for continuous outcome variables and the logistic regression model for dichotomous variables.

The medical center where the operation took place will be examined as a confounder to account for differences in the populations treated at each cardiothoracic unit, in the medical approach implemented, and in possible effects on outcomes.

For investigation of the second goal, we will compare those who did and did not participate in a CR program using the same tests as for comparison of control and intervention groups. We are aware that participation or non participation in CR depends on other parameters and can not be considered as randomly assigned. Therefore, we will apply the propensity score approach. First we will build a model for the probability of participation in CR (i.e. the propensity score) that will be based on a set of demographic and medical variables. This propensity score will be used in the regression analysis of the effect of participation in CR on various outcomes.

### Ethics

The study was approved by the IRB of the Sheba Medical Center and of each participating medical center. An informed signed consent was obtained from all participants prior to the first interview. Data confidentiality has been maintained in accordance with current regulations.

The study is registered in ClinicalTrials.gov as NCT00356863.

## Discussion

Since our planning and launching of this study, considerable evidence has accumulated about the benefits of cardiac rehabilitation (CR) [19], as well as about low participation rates in CR programs [20-22]. Interventions have focused on means of increasing referral rates. Referral strategies have been categorized as 'automatic' (by electronic health records or systematic discharge); 'liaison' (discussions with health-care providers), and 'other' (such as written material and phone calls) [23]. A recent review concluded that automatic referral orders attain the highest referral rates, and a combination of automatic and liaison methods attain the highest rates of CR enrollment [24]. In a recent Canadian study, automatic referral and liaison methods, alone, and even more so when combined, considerably increased CR participation [23]. Increasing physician awareness of the benefits of CR has also been shown to increase patient participation [25].

Guidelines issued in 2007 by the American Association of Cardiovascular and Pulmonary Rehabilitation (AACVPR), the American College of Cardiology (ACC), and the American Heart Association (AHA) recommend automatic referral to cardiac rehabilitation for every eligible patient [26]. In April 2011, the Canadian Association of Cardiac Rehabilitation (CACR) and the Canadian Cardiovascular Society (CCS) issued a joint position statement recommending a combined approach to increasing CR participation, consisting of a checklist or electronic referral and talking with patients [23].

### Study strengths

This large prospective study was carried out in four languages in five medical centers across Israel. We designed a simple and low cost intervention that combined the primary elements that have since been recommended for increasing CR referral, as delineated above: automatic referral; liaison; written material and phone calls to patients; and increasing awareness of physicians. We conducted a comprehensive assessment, with a relatively long follow-up, of clinical, psychosocial and sociodemographic patient outcomes, and collected considerable data of the CR programs attended.

### Methodological considerations

We made every effort to include all eligible patients in the study, and collected data on eligible patients who were not recruited. We note that there were no differences in mean age or gender distribution between the participating and non-participating CABG patients (Table 1). The main reasons for not participating in the study were refusal and logistical problems, mostly due to the inability to coordinate an interview before CABG surgery.

Unlike many studies on intervention programs that use referral rate or rate of enrollment as their end-point, we assessed actual participation in CR programs.

The sequential recruiting of the control and interventional arms ensures identical settings. However, though no CR interventions were conducted during recruitment of the control arm, we cannot ignore the possibility that awareness of the medical staff to the benefit of CR may have increased during that period by means other than by our intervention.

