#### Calculation of sample size and study duration

We calculated sample size to enable detection of significant differences between patients in the intervention and control arms in the rate of participation in CR. We used estimates for these rates from published data on self-reported participation in CR in post-CABG patients [8]. The calculations for power, comparing the proportions [13] of participation in rehabilitation in the two arms, using a two-sided test with significance alpha = 0.05 and size of groups n1 = n2 = 430, and assuming that the proportional CR participation rate at baseline is 7%, yielded 90% power to detect a difference of 7% following intervention (that is, a rehabilitation rate of 14% in the intervention group). We assumed that up to 15% of the sample would fail to complete all the study items. Therefore, we increased the sample size accordingly to compensate for missing values. Thus, the targeted total for the intervention and control arms were 500 patients each, or 1000 in total.

According to data provided by the Israeli Ministry of Health, a total of 1596 CABG operations were carried out in the five units participating in the study during the year 2003. Assuming that these figures remained stable, and that exclusion criteria and refusal rate would reduce potential participation by 40%, we expected to reach our target sample of 1000 CABG patients (including pilot sample) within 15 months from study initiation. In reality, study was initiated in the five units at different times, as after the Institutional Review Board (IRB) approvals were obtained. As a result, the total duration of patient recruitment was longer than initially anticipated. The first 520 patients who enrolled in the study (from January 2004 to May 2005) composed the control arm. The following 504 patients, recruited between June 2005 and November 2006, composed the intervention arm (Figure 1).

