#### One year follow up interview

Participants were approached again for a second interview one year after CABG surgery. Interviews were carried out by trained interviewers at participants' homes. The assessment included an interview and obtaining anthropometric measures and medical information from medical documents. Assessment at both time-points took approximately 60 minutes to complete. Patients were asked to prepare medical documentation for the interview. Those refusing a home interview were contacted by telephone; they provided information only regarding their attendance in a CR program (n = 118).

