#### Intervention

We first asked physicians and nurses in each participating cardiothoracic unit to complete a short questionnaire to assess their level of knowledge regarding the content and provision of CR programs within the Israeli national healthcare system. This was followed by a one-hour seminar that included information for medical staff on the potential benefits of cardiac rehabilitation for patients and the provision of these programs within the healthcare system in Israel.

Recruitment and interviewing of the intervention arm was identical to that described for the control arm. In addition, patients in the intervention arm participated in an educational program that included 4 elements:

1. An individual 10-minute consulting session conducted during the hospital stay, prior to CABG surgery. We explained the benefits of cardiac rehabilitation, the content of such programs, criteria for patient eligibility for CR under the Israeli National Health Insurance Law, and the contact details of CR programs available in Israel and of the health maintenance organization (HMO) to which patients were affiliated. Sessions were delivered in Hebrew, English, Russian, and Arabic.

2. Pamphlets specially prepared for this study, in Hebrew and Russian, were distributed to patients at the end of the consultation session. The content was the same as that presented orally.

3. The director of each participating cardiothoracic ward was asked to issue each patient an explicit recommendation for participation in a CR program in their letter of discharge.

4. Two to three weeks after discharge from the hospital, each patient received a telephone call from a trained interviewer inquiring whether he or she intended to participate in a CR program. Patients were reminded of the importance of CR, and further encouraged to participate.

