#### Validation of patient interviews

To verify and complete information on medications and comorbidities, as well as the respondents' self report on medical parameters, each interview was supplemented by information from patients' medical records: medical files, and medical documentation.

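### The primary endpoint rests on patient report, the described validation does not name it, and only the intervention arm was urged to attend, so over-reporting could differ by arm

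*Protocol article*

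**What the plan says.** The main outcome for the comparison of arms is CR participation at one year (Main outcome variables). It is obtained by trained interviewers at a home visit for which patients were asked to have medical documents ready. Of those who declined the visit and were telephoned, the article says "they provided information only regarding their attendance in a CR program (n = 118" (One year follow up interview).

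A separate section, Validation of patient interviews, gives the purpose of the record check: "To verify and complete information on medications and comorbidities", together with self-reported medical parameters. CR attendance is not named there, and no check against programme or health maintenance organization (HMO) records is described elsewhere.

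The Intervention section gives the intervention arm, and not the control arm, a counselling session, pamphlets and a request for a referral in the discharge letter. Two to three weeks after discharge, "each patient received a telephone call from a trained interviewer", who asked about the patient's intention and encouraged attendance. No separation between the callers and the outcome interviewers is stated.

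Under Methodological considerations the article sets its endpoint apart from referral and enrolment rates: "we assessed actual participation in CR programs". That section discusses rising staff awareness over time as a limitation. It does not mention reporting bias.

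**The concern.** One arm was told by the study that CR is important, was telephoned about it, and was later asked by the study whether it had attended. The other arm was only asked. A patient who did not attend has more reason to give the welcome answer in the first situation than in the second. Misreporting that is equal in both arms mainly costs power. Misreporting that is greater in the intervention arm adds directly to the estimated effect.

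The planned rates make the comparison sensitive to this. At a 7% base rate, 93% of patients can give a false yes, so a small proportion of false answers is large beside a planned difference of 7 points. The same variable also defines the exposure in the second analysis (participants against non-participants), and a propensity score does not repair a misclassified exposure.

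**Working it through.** **Inputs** (Calculation of sample size and study duration):
- "using a two-sided test with significance alpha = 0.05 and size of groups n1 = n2 = 430"
- "assuming that the proportional CR participation rate at baseline is 7"%
- "a rehabilitation rate of 14% in the intervention group"
- "yielded 90% power to detect a difference of 7% following intervention"
- Recruited: 520 control, 504 intervention, 1024 in total. Telephone-only: 118.

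**Assumption, not in the documents:** a proportion f of intervention-arm non-attenders report attending. Control-arm false yes answers and under-reporting in both arms are set to zero.

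**Step 1: reproduce the plan's sample size.** With p1 = 0.07, p2 = 0.14, mean 0.105 and d = 0.07:

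n = [1.960 × √(2 × 0.105 × 0.895) + 1.282 × √(0.07 × 0.93 + 0.14 × 0.86)]² / 0.07² = 401 per arm.

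The continuity correction, n/4 × [1 + √(1 + 4/(n × d))]², gives 430, the stated figure. Without the correction, 430 per arm has 91.9% power. The sample size is not in question.

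**Step 2: spurious difference when there is no true effect.** True attendance is 7% in both arms. The reported intervention rate is 0.07 + 0.93f, so the spurious difference is 0.93f.

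**Step 3: chance of a significant result.** Two-sided z-test, 430 per arm, pooled standard error SE0 under the null and unpooled SE1 under the reported rates:

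P = 1 − Φ[(1.96 × SE0 − 0.93f)/SE1] + Φ[(−1.96 × SE0 − 0.93f)/SE1].

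For f = 2%: the reported rates are 7% and 8.86%, and SE0 and SE1 are both about 0.0184. The first argument is (0.0361 − 0.0186)/0.0184 = 0.95, which gives 0.171. The other tail adds about 0.001. The total is 17.2%.

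| f | reported intervention rate | spurious difference (points) | chance of significance |
|---|---|---|---|
| 0% | 7.0% | 0 | 5% |
| 1% | 7.9% | 0.9 | 8.1% |
| 2% | 8.9% | 1.9 | 17% |
| 3% | 9.8% | 2.8 | 31% |
| 4% | 10.7% | 3.7 | 48% |
| 5% | 11.7% | 4.7 | 65% |
| 7.5% | 14.0% | 7.0 | 92% |

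The last row is f = 0.07/0.93, at which misreporting alone produces the whole planned effect. Against 7% in the control arm, the smallest significant intervention count is 47/430 = 10.9%, reached at f of about 4.2%.

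**Step 4: contrast with equal misreporting.** If 2% of non-attenders in both arms give a false yes, 7% against 14% becomes 8.9% against 15.7% and power falls from 91.9% to 86.6%. At 5% in both arms it falls to 78.1%. Equal misreporting weakens the comparison but does not create an effect.

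**Step 5: scale of the checking.** Expected reported attenders at the planned rates are 430 × 0.07 + 430 × 0.14 = 90, or 520 × 0.07 + 504 × 0.14 = 107 on the numbers recruited. Telephone-only patients are 118/1024 = 11.5%. At the mean planned rate about 118 × 0.105 = 12 of them would report attending.

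**The case against.** Several points on the other side stand.

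- **The word actual.** A reader might infer that the article claims record-verified attendance and so contradicts itself. It does not: the sentence contrasts attending with being referred or enrolled, and in that sense it is fair. Nor is self-report foreign to the plan, since the planning rates are described as self-reported.
- **Unchecked.** The validation section does not name CR attendance, but no section says attendance went unchecked. Each interview was supplemented from medical records, and documents were requested for home visits. Some attendance may have been confirmed incidentally, though no rule for doing so is described.
- **Safeguards.** Patients reporting attendance were to be asked about programme type, content, adherence and co-payment, which makes a false yes harder to sustain. Interviewers were trained and interviews quality-assured. About a year separates the call from the outcome interview.
- **Same interviewers.** A reader might infer that the person who encouraged the patient also recorded the outcome. The documents show the same role, not the same individuals.
- **Telephone-only patients.** Their split by arm is not given, so no bias between arms follows from the number 118. Setting 118 respondents against about 90 attenders would not compare like with like. Telephoning patients who refused a visit also reduces missing outcomes.
- **Replacing the endpoint.** Recruitment ended in November 2006 and the article cites a 2011 statement, so one-year data were already collected. Making confirmed attendance primary at that stage would be hard to defend, and incomplete records would turn true attenders into non-attenders.

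These points limit the claim and the remedy. They do not remove the asymmetry: one arm was urged to attend, the described validation does not name the primary endpoint, and telephone-only patients gave attendance without the supporting details.

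**Conclusion.** The point holds as a vulnerability, not as a demonstrated bias. The primary endpoint, as described, is patient-reported, its corroboration is not part of the stated validation, and the two arms had different reasons to say yes. Differential over-reporting is plausible, would favour the hypothesis, and is not acknowledged as a limitation.

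Its size is unknown. The 17% to 65% range rests on an assumed 2% to 5% of false yes answers in the intervention arm only, no under-reporting, and the plan's own 7% rate and 430 per arm. At 1% the effect is small (8.1%). A reader might conclude that a positive result would be an artefact, or that the endpoint must be replaced. The documents support neither. They support naming the endpoint for what it is and testing how far the result depends on uncorroborated answers.

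**What to change.** 1. Keep reported participation as the primary endpoint. In Methodological considerations, call it self-reported participation, keep the contrast with referral and enrolment, and list differential reporting as a limitation.
2. Extend Validation of patient interviews to reported CR attendance. Use the documents patients prepared for the home visit and the programme type, adherence and co-payment details already collected, with programme or HMO records where they can be accessed.
3. Add a sensitivity analysis that counts only corroborated attendance, with the rule for corroboration written down beforehand and applied identically in both arms.
4. Report the number of telephone-only answers by arm and repeat the primary comparison without them. This also guards the analysis in item 3, because telephone-only patients have no home-visit documents and would fail corroboration more often for that reason alone.

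Cost: modest checking of about 90 to 110 reported attenders, and a somewhat lower corroborated rate where documents are incomplete. Checking only reported attenders does not detect under-reporting, which is a further reason to keep this analysis supportive. Access to programme or HMO records is not described in the article. If it cannot be obtained, the rest of the fix can still be done with information already collected.

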#### Design

A controlled prospective study (Figure 1). The control arm comprised 520 patients who underwent CABG surgery between January 2004 and May 2005 in five medical centers across Israel. The intervention arm comprised 504 patients recruited from the same cardiothoracic departments between June 2005 and November 2006. Since the intervention included a seminar for the cardiothoracic unit staff, all patients in the control arm were recruited first. To avoid contamination, the implementation of our intervention and recruitment of the intervention arm took place upon completion of the control phase. In both arms, we approached consecutive patients scheduled for CABG surgery. Consenting patients were interviewed before surgery and one-year post surgery. The intervention group received oral and written explanation about CR programs and a telephone call after hospital discharge. In addition, the medical staff attended a one-hour seminar on CR and it was recommended that referral to CR be added to the patient letter of discharge. The control group received no additional treatment beyond usual care.

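### Arm coincides with calendar period, so the claim that sequential recruitment gives identical settings is wrong for anything that changes over time, and the analysis section does not take up the secular threat the article concedes

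*Protocol article*

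**What the plan says.** - **Allocation by date.** Under Calculation of sample size and study duration: "The first 520 patients who enrolled in the study (from January 2004 to May 2005) composed the control arm". The next 504, recruited June 2005 to November 2006, formed the intervention arm. The Design section gives the reason: to avoid contamination through the staff seminar, "the implementation of our intervention and recruitment of the intervention arm took place upon completion of the control phase".
- **Staggered starts.** The sample-size section also reports that "study was initiated in the five units at different times", following ethics approvals.
- **Claim of comparability.** Methodological considerations: "The sequential recruiting of the control and interventional arms ensures identical settings". The next sentence concedes that staff awareness of CR may have risen in the control-recruitment period for reasons other than the intervention.
- **Analysis.** Methods for statistical analysis presents the first comparison as the impact of the intervention on CR uptake. It plans univariate tests and logistic regression adjusted for risk factors and potential confounders. On centre: "The medical center where the operation took place will be examined as a confounder", to account for differences between units. Calendar time is not named.

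**The concern.** Using the same five units holds the place constant but not the time. The intervention began only after control recruitment had finished, so at no date are both conditions observed together, and period and arm cannot be separated by design. A claim of identical settings is then wrong for every factor that changes with time, such as staff awareness, referral habits, programme supply and insurance cover.

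The article supplies its own reason for caution. It concedes the awareness trend, and its Discussion says that much evidence on CR has accumulated since the study was planned and launched. The effect of the intervention on attendance is the study's first objective. If usual-care uptake was rising, part or all of that rise would be credited to the intervention. If centres with different uptake contribute different shares to the two arms, that difference is added too unless centre is in the model.

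**Working it through.** **1. The plan's own figure.** Inputs from the sample-size section: 7% versus 14%, two-sided alpha 0.05, 430 per arm, 90% power. The standard two-proportion formula with continuity correction gives n = 430 per arm and power 90.1%. Without the correction, n = 401 and power at 430 is 91.9%. The stated calculation reproduces and is not at fault.

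**2. Distance between the arms in time.** Control period 17 months, intervention period 18 months. Distance between midpoints = 17/2 + 18/2 = 17.5 months.

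**3. Effect of a secular rise.** Expected arm difference = true effect + (usual-care rate in period 2 − usual-care rate in period 1). The drift is added in full, whether or not the test is significant.

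Assume no true effect, p1 = 7%, p2 = 7% + drift d, and n = 430 per arm. With pooled rate p, s0 = √[2p(1−p)/n] and s1 = √[(p1(1−p1) + p2(1−p2))/n], the chance of significance in favour of the intervention is Φ[(d − 1.96·s0)/s1]. The table adds the small opposite tail.

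Example, d = 3 points: s0 = √(2×0.085×0.915/430) = 0.01902; s1 = √((0.0651 + 0.0900)/430) = 0.01899; Φ[(0.03 − 0.0373)/0.01899] = Φ(−0.383) = 35%.

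| Assumed rise between arms (points) | Per year (×12/17.5) | Significant, 430 per arm | Significant, 520 vs 504 |
|---|---|---|---|
| 0 | 0 | 5% | 5% |
| 1 | 0.7 | 9% | 9% |
| 2 | 1.4 | 19% | 22% |
| 3 | 2.1 | 35% | 41% |
| 4 | 2.7 | 54% | 61% |

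The smallest significant observed difference at 430 per arm is about 4 points (30 versus 47 participants; 17/430 = 3.95 points).

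**4. Effect of a shift in centre mix, if centre is left out of the model.** Assume two equal groups of centres averaging 7%. Bias = shift in mix × difference in rates.

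- Rates 4% and 10%: a shift of 10 or 20 points gives 0.6 or 1.2 points (significant in 6% or 11% of trials).
- Rates 2% and 12%: a shift of 20 or 30 points gives 2 or 3 points (21% or 41%).

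Table 1 gives centre totals but not centre by arm, so the actual shift is unknown.

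**5. Cost of a linear time term.** With uniform accrual over 35 months, the squared correlation of arm with time is (17.5²/4)/(35²/12) = 76.6/102.1 = 0.75. Variance inflation = 1/(1 − 0.75) = 4.

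- Power for 7% versus 14% at 430 per arm falls from about 92% to about 39% (logistic simulation with 1,500 replicates: 38%).
- 90% power would need 4 × 401 = 1,604 per arm.
- Under linear rises of 2 to 4 points, the simulated false-positive rate of the step returns to about 4–6%.

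**6. Can the step estimate act as a gate?** With a true 7-point effect and no trend, the simple estimate has SE √((0.0651 + 0.1204)/430) = 2.08 points, and the step estimate about 2 × 2.08 = 4.2 points. Their difference has SD √(4 − 1) × 2.08 = 3.6 points. It exceeds 3.5 points in either direction with probability 2[1 − Φ(3.5/3.6)], about one time in three.

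**The case against.** Five points on the other side deserve weight.

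- **The design is reasoned and the threat is disclosed.** A unit-level seminar makes concurrent controls in the same ward hard to keep clean, and the article admits the awareness trend. No model can now supply concurrent controls. This stands. It does not rescue the sentence about identical settings, which is a positive statement and incorrect for time-varying factors.
- **This is an article, and an analysis plan may exist.** Exact model terms are commonly left to it. A reader might infer that the investigators have no plan for time at all; the article cannot establish that. What can be said is that its analysis section addresses non-random participation with a propensity score for the second comparison and does not take up the conceded trend for the first.
- **Centre is not ignored.** A reader might infer that centre is treated as optional. The text singles it out as a confounder and gives the purpose. The narrower point is that examining it does not fix it as a term.
- **Imbalance by centre is not shown.** A reader might infer that late-starting units are under-represented among controls. No start dates or centre-by-arm counts are given. The totals do not suggest a depleted control period: 520/17 = 30.6 recruits per month against 504/18 = 28.0, and 520/1401 = 37% of all bypass patients recruited against 504/1410 = 36%. These totals cannot exclude a shift in mix.
- **The trends are assumed.** A reader might infer that a modest drift would be declared an effect, or that the 5% error rate fails outright. Neither follows. A rise of 1 or 2 points is non-significant in most trials, and about 4 points is needed for an even chance. From a 7% base, 2 points per year is already a relative rise of 2/7 = 29% per year. The article also reports no directed CR action in the units before the study and no CR interventions during control recruitment.

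**Conclusion.** The point holds in a limited form. Full confounding of arm with calendar period follows from the stated recruitment dates and needs no assumption. The claim of identical settings is therefore wrong for time-varying factors, and the article's analysis section does not act on the threat conceded in the next sentence.

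The size is conditional. Any drift biases the estimate one for one. Rises of 1 to 4 points, assumed from 7% with 430 per arm and no true effect, could give significance in about 9% to 54% of trials. The documents state no trend, so its presence, direction and size are unknown. Centre mix is the smaller and removable part: 0.6 to 3 points under the assumed scenarios, and only if centre is left out.

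The documents do not support the conclusion that a positive result would be spurious, nor that adding a time term would cure the design.

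**What to change.** 1. **Centre.** Include centre as a fixed term in the primary logistic comparison, or stratify by centre, whatever a confounder screen shows. Report centre mix by arm.
2. **Trend, as a sensitivity analysis only.** Fit a logistic model with centre, surgery month (linear) and a step at June 2005. Report the control-phase slope and the step with its confidence interval. Do not make attribution depend on the step agreeing with the simple estimate: at about 39% power, such a rule would often discard a real effect.
3. **Drift needed to explain the result.** State it beside the main estimate. If 7% versus 14% were observed at 430 per arm, the lower 95% limit would be 7 − 1.96 × 2.08 = 2.9 points. A drift of 2.9 points (2.9 × 12/17.5 = 2.0 per year) would bring that limit to zero, and a drift of 7 points would explain the whole difference.
4. **Wording.** Replace the sentence on identical settings with a statement that the same units were used but the effect is confounded with period, and word the conclusion to match.

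Cost: a little extra modelling on recruitment and surgery dates the study should already hold, an imprecise sensitivity estimate, and a more cautious conclusion. No new data are needed.
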